### Phase 2 [implementation and evaluation of the refined model (Mref)]

This phase aims to implement the model (Mref) across all educational institutions over a period of 12–18 months. This shall be aimed primarily in collaboration with the district education and health authorities with research investigators mainly providing advisory and supportive roles. Guidelines, protocols and training material will be adapted to identify and train an implementation team at each institute for rolling out of the Mref model (Figure 4).

**Figure 4 fig4:**
[figure not shown]
Flowchart for implementation and evaluation of Mref model.

Implementation at each cluster will engage administrative authorities/heads of institutes along with volunteering gatekeepers and youth champions who will be intensively trained to implement the Mref model. Throughout phase 2, both the district education and health system will be supported to conduct capacity building of school and college administrators; teachers and youth champions and health care professionals to handle referrals of high risk students. This phase involves following key activities:

Expansion and engagement of resources and staff within the district education system; educational institutes and district health systems including private practitioners will be done through a series of consultative meetings with district education and health system.Consultative meetings with administrative heads and district government agencies to develop standardized guidelines and protocols for management of suicide prevention at the institutes.Data on implementation and clinical outcomes will continue to be collected via the research team along with conducting bi-monthly meetings with the implementation teams to provide supervision, feedback and troubleshooting implementation challenges. The selection of assessment measures has been guided by the suitability of measures for the target group and purpose, brevity of the measures, cultural appropriateness, and prior utilization in the Indian context.

#### Tools for use for gatekeepers

Knowledge and self-efficacy survey (43): The questions of the scale are derived from a gatekeeper training survey developed by QPR institute and the research on effectiveness training (44). The four items on knowledge include question on asking directly about suicidal thoughts, understanding that they want help, knowledge on the potential to help them even when they have made suicide plans and identification of warning signs. These were selected and phrased to reflect suicide prevention facts that are most relevant to gatekeeping. The questions are answered as ‘no’ ‘maybe’ or ‘yes’. with “no” coded as 1 and “yes” coded as 3. There are 3 questions on self-efficacy which include Comfort in asking, preparedness to connect to help and confidence as to where to refer. The questions are answered on a Likert scale (4-point) varying from “not very,” “somewhat,” “very,” to “extremely.” The final self-efficacy score is obtained by adding individual item scores. In addition, an item on Intent to ask (45) will be included to assess respondents’ likelihood (i.e., intent) of asking someone who appears to be at risk or have thoughts of suicide, using a 5-point Likert-type scale.Gatekeeper help giving behaviors. These would include the following items using a specified time frame (last 3 months) (a) whether or not a respondent believes he/she had encountered someone who seemed to be in psychological distress (Yes/No/do not know or maybe) (45), (b) number of times they asked someone they recognized as possibly suicidal, directly/indirectly, if he or she had been thinking about suicide (45). In addition, the following additional questions on gatekeeper behaviors would be asked (43). (1) The number of individuals who approached the gatekeeper with thoughts or feelings of suicide; (2) the number of youth whom the gatekeepers themselves had approached regarding potential suicidal ideation and (3) the actions taken by gatekeepers based upon these conversations (43).

#### Tools for youth champions and youth beneficiaries

Patient Health Questionnaire (PHQ)-9: The present study will also be using a 9-item self-report version of the Primary Care Evaluation of the Mental Disorders (PRIME-MD), a validated screening tool for identifying levels of depression among individuals (46). It is composed of 9 items to capture depressive symptoms. The total scores may range from 0 to 27 and five levels of severity varying from minimal (0–4), mild (5–9), moderate (10–14), moderately severe (15–19) and severe (20–27) (46).Perceived Stress Scale (PSS-10): A 10-item self-reporting screening tool for identifying level of personal stress and the degree to which an individual appraises their daily life circumstances as stress-inducing (47). The total score is the sum of all items, including reverse scoring for positive items (item 4, 5, 7 and 8). The total score ranges from 0 to 40 and three levels of severity ranging from low (0–13), moderate (14–26) and high (27–40) (47).Mental Health Awareness. This 19-item measure, with each item comprising three response options: false/true/do not know. ‘True’ responses to correctly worded items from this section receive a score of one, while ‘true’ responses for incorrectly worded items receive a score of zero. This is reversed for three items (items). ‘Do not know’ as a response to any item is given a score of zero. It was developed as part of a larger study on promotive intervention in college youth, in an Indian setting, via an extensive literature review, content validation by experts and 3 pilot trials covering 238 college going youth. The measure exhibited satisfactory reliability and its scores correlated positively with the measure of attitudes toward mental health and illness and showed significant changes following participation in a promotive intervention (48). Two additional items (myths/facts) pertaining to sadness vs. depression and usefulness of help seeking when distressed are planned to be included in addition (38).General Help Seeking Questionnaire (GHSQ): Help seeking inclination refers to the likelihood of seeking help from one or more sources for psychological distress (49). The tool assesses the participant’s intention to receive aid from varied sources as well as the inclination to reject /not seek help from any source (help negation). GHSQ is a flexible tool, allowing researchers to make modifications as per study requirement for instance, adapting sources of help and types of problems/issues to enhance relevance for the target population. Seven to twelve sources have been listed in previous studies and psychometric properties (internal consistency, convergent validity) have been found to be satisfactory across studies (50, 51). A 7-point Likert scale is used for ratings for each of the potential sources, varying from 1 (Extremely Unlikely) to 7 (Extremely likely) (49). In the present study, help seeking preferences from both formal and informal sources (e.g., teachers, counselors, helpline numbers, peer, guardian etc.) for emotional distress will be examined along with the item on help negation. In addition, an open-ended item for any other sources of help will be used to capture any unlisted source.Actual Help-seeking Behavior: This would be captured by enquiring about help sought within a specified time frame from one or more of the listed sources for personal/emotional problems. The list of sources would match the sources used in GHSQ. The assessment would use a checklist of items and the youth would also be given an option to briefly mention the type of issue/distress prompting the help-seeking behavior (50).Helping Giving Behaviors: Multiple choice questions would be used for the present study to assess if the youth encouraged someone who may have been experiencing mental health concerns to reach out for professional help (No, 1 person, 2 persons, more than 2 persons). Additionally, they would be asked if the encouragement provided actually led to the person seeking help (yes/No/not sure) (52).

#### Other tools

Acceptability, appropriateness, feasibility of intervention measure: The implementation outcomes of the present study will assessed across three measures ‘Acceptability of Intervention Measure (AIM)’, ‘Intervention Appropriateness Measure (IAM)’, and ‘Feasibility of Intervention Measure (FIM)’ (53). The 5-point Likert scale comprises 12 items (4 items for each construct), with responses varying from ‘completely disagree’ (score 1) to ‘completely agree’ (score 5) for each item (53). This will be used with gatekeepers, youth champions and beneficiaries with a focus on ascertaining acceptability, appropriateness and feasibility of gatekeeping, conducting universal campaigns and activities and overall promotive program, respectively.Reach (exposure) and feedback: The youth beneficiaries would be enquired if they were exposed to and participated in any mental health promotion program event/initiative within the specified period.Feedback questions will be developed for gatekeepers, youth champions as well as youth beneficiaries to document overall acceptability of the program, perceived gains, if any as well as likelihood of recommending to others/participating in future.Semi structured interviews: Semi structured interview probes will be developed for use with leaders/coordinators (IDIs), youth champions and gatekeepers (FGDs) to document barriers as well as enablers for implementing the intervention components and overall acceptability of the program

#### Assessment time-points

The gatekeeper tools will be used at baseline (before gatekeeper training) and at 3 months intervals. In addition, all the tools except Gatekeeper help giving behaviors will also be used immediately after the training (post training assessment). Similarly, all the tools for youth champions and youth beneficiaries will be used at baseline (before the youth champion training) and subsequently at three-month intervals. In addition, these tools (except helping and help giving behaviors) will also be used immediately following the training for youth champions (post-training assessment). The general tools will be used at a three-month interval after the gatekeeper training and youth champion training are completed as described in Table 3.

**Table 3 tab3:** Description of study timelines for assessments.

Participant	Variables	T1 (Baseline)	T2 (4–6 months after T1)	T3 (12 months after T1)	T4 (18 months after T1)
Gatekeepers	Knowledge, Self-Efficacy, Intent to Ask	✓	✓	✓	✓
	Help-Giving Behaviors	✓	✓	✓	✓
Youth beneficiaries and youth champs	Depressive Symptoms (PHQ-9)	✓	✓	✓	✓
	Perceived Stress (PSS-10)	✓	✓	✓	✓
	Mental Health Awareness	✓	✓	✓	✓
	Help-Seeking Inclination (GHSQ)	✓	✓	✓	✓
	Help-Seeking Behavior	✓	✓	✓	✓
	Help Giving Behaviors	✓	✓	✓	✓
General	Acceptability, Appropriateness, Feasibility (AIM, IAM, FIM)	✗	✓	✗	✗
Exposure to program components and feedback	–	✗	✓	✓	✓
Semi-structured interviews (Barriers/Enablers)	IDIs/FGDs	✓	✓	✓	✓

### Implementation strategies

Successful implementation of any intervention program/model is dependent on appropriate and strategic use of strategies that can facilitate adoption, use and sustainment of the program. Implementation strategies target individual and contextual level mechanisms that are likely to influence implementation processes and implementation outcomes (54, 55).

The present study will be guided by the compilation of School Implementation Strategies, Translating ERIC Resources (SISTER) (56) that adopted the taxonomy of ERIC strategies (Expert Recommendations for Implementing Change) to educational settings. Examples of potentially useful SISTER strategies relevant to the context of this implementation project include leveraging policy and guidelines, empowering leaders, identifying implementation facilitators and barriers, building local partnerships, training and supporting implementers and improving buy-ins and motivation, developing educative materials, facilitating interactive problem solving, audit and feedback. The final choice and mix of strategies would be based on the local context/settings of implementation and these are also likely to be dynamically used/adapted based on continuous field observations during implementation. The strategies and processes related to implementing the intervention package for present study are entailed in Table 4.

**Table 4 tab4:** Implementation outcomes and data sources.

Implementation outcome	Institute-level measure	Youth-champ level	Teacher gatekeeper level	Data source/Method
Adoption: Intention, initial decision, or action to try or employ the intervention/uptake	Number of institutes approached. Number of Expression of interest received Number of institutes finally enrolled. Number of institutes with full implementation Number of institutes with partial implementation (implementation of 50% or more or less than 50% of intervention components)	Success of recruiting desired number of youth champions per institute depending on target number of sections/classes (Minimum 2 per class)	Success of recruiting and training desired number of teachers per institute depending on size of target population of students (30% of teachers teaching the target population)	Administrative data and records
Reach: The number and proportion of individuals who are exposed to and participate in a program	—	Number and proportion of youth champs who engage in the program The number/proportion of youth beneficiaries who are reached/exposed to the program	Number and proportion of gatekeepers who engage in the program	Responses from the target population (youth beneficiaries) regarding exposure to, participation in the intervention programs conducted, and awareness about nature of resources made accessible and how to access the same
Appropriateness: Perceived fit, relevance to address a particular issue	–	Appropriateness of campaign -based intervention	Appropriateness of campaign-based intervention and gatekeeper intervention	Intervention Appropriateness Measure (IAM)*
Feasibility: The extent to which the program can be successfully carried out within a given setting	Overall feasibility of implementing intervention package at institutes	Feasibility of campaign -based intervention	Feasibility of campaign -based intervention and gatekeeper intervention	Feasibility of Intervention measure (FIM)* (Youth champs, gatekeepers) Interviews with leaders and coordinators at institutes Field observation notes
Fidelity: Degree to which the intervention was implemented as planned	–	Sampling of universal campaigns conducted (direct observations/records of the same)	Examination of data on gatekeeper behaviors measure	Observations, Gatekeeper behaviors data and Other relevant logs/records, e.g., referrals made following identification of high distress
Acceptability: Perception of stakeholders that a given intervention is agreeable	Leaders/Coordinators’ Views	Rated by Youth champs and sample of beneficiaries: Universal programs/Campaigns	Rated by gatekeepers about gatekeeping intervention	Acceptability of Intervention measure (AIM)* plus additional feedback items Interviews with leaders and coordinators (Regarding overall package)
Implementation cost				Pragmatic approach by Cidav et al. (62) **
Effectiveness	Mean score of: Depressive symptoms-PHQ-9 Perceived stress-PSS10 Help seeking inclination-GHSQ Help-Seeking Behavior	Proportion of youth champions who were approached by distressed students for help Proportion of distressed students referred by youth champions to gatekeepers or school leaders Proportion of students who accessed self - help modules	Proportion of gatekeepers who were approached by distressed students for help Proportion of distressed students referred by gatekeepers	Administrative data and records self-reported/log books maintained by gatekeepers and youth champions
Sustainability: Extent to which the intervention is maintained/institutionalized	Key informant interviews by district authorities and leaders			Testimonials by gatekeepers and youth champions and youth beneficiaries if possible

**Described in detail under statistical analysis heading.

### Study outcomes

#### Primary outcomes

The present study focuses on the following primary outcomes:

Reduction in suicide risk factors: This is measured by a decrease in perceived stress levels and depressive symptoms among students in educational institutions using validated scales.Improvement in help-seeking behavior: This is measured by a rise in the proportion of individuals engaging with services/aid for mental health.

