The psychological risk factors are broadly organized into affective, cognitive, and social processes. Affective processes such as low self-esteem, worthlessness, neuroticism, hopelessness, difficulty in identification of emotions, ineffective emotional regulations, result into persistent and elevated risk of suicidal behavior in youth (6). Also, the cognitive processes such as impulsivity-aggression traits, selective-information processing are the predictors of suicidality among youths. The social processes such as loneliness (often mediated by other psychopathologies such as depression, anxiety) are associated with suicidality among youth (5).

In addition, recent advances in the literature suggest that psychiatric comorbidity further exacerbates suicide risk. Anxiety and depressive symptoms are significant predictors for the onset of suicidal ideaton and attempts among youth (7). Furthermore, individuals with multiple co-occurring mental health conditions exhibit substantially higher vulnerability to suicidal behaviors as compared to those with a single diagnosis (8). These findings underscore the compounded risks faced by individuals, particularly youth, who struggle with multiple mental health issues.

There is substantial evidence highlighting socio-environmental risk factors associated with youth suicide. These include child/adolescent maltreatment (any form of child abuse-physical, sexual or emotional), bullying (including cyberbullying) (9), peer and media influence, media reporting, drifting (getting disconnected from one’s support system-e.g. school, family), family constellation (disrupted family, parental loss may be due to death or divorce) (10), exam related factors (e.g., pressure to perform, failure, anxiety), minorities/ethnicity/caste-based discriminations, availability of lethal means, gender identity and sexual orientation, perceived stigma and availability of mental health resources (5).

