### Sample size for individual level effectiveness

The sample size for youth beneficiaries is calculated to detect a 0.20 effect size{Anticipated per SD effect size(reduction in depression score) = 0.2 (Baseline mean = 8.5; Endline mean = 7.5, SD = 5.0; ES/SD = 1/5 = 0.2)} in mean on the PHQ-9 score in a group (90% power, 2-sided 5% significance level), assuming a correlation of 0.5 between T1 (Baseline) and T4 scores (3 measurements, 6, 12 and 18 months from baseline), and non-response rate of 10%, The required sample size will be 400 students per strata (i.e., 400 for schools, and 400 for UG/PG college) of selected educational institutes.

Average size of the class per stratum could be used to determine the number of classes to be randomly selected from each stratum (e.g., if the average class size for 9 th and 10 th grade is 40, then (400/40 = 10)10 classes would be required to get the sample of 400 in this stratum). The unit for sampling at the college could be batch/year of study and a similar approach could be used to determine the number of units to be followed up.

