### Phase 1 (optimization of model M0+)

The primary objective of this phase is implementation of the initial intervention model via iterative cycles.

Each study site expects at least 3–4 cycles of model optimization followed by implementation, evaluation and refinement to reach a scalable high coverage model. During each cycle, lasting 2–3 months, data will be collected on a subsample of 4–6 clusters of educational institutes in the district from leaders, gatekeepers and youth beneficiaries via in-person and online administration of questionnaires. The data shall be collected on both clinical and implementation outcomes, at baseline and at an interval of 2–3 months of model implementation. The outcomes of the phase 1 will guide in identifying the most promising model for scalability (Mref) and also entail the following:

Adaptation of training materials: Training manuals for leaders, gatekeepers and youth shall be adapted to meet specific and contextual relevance for the selected study districts along with the development of self-help and prevention resource materials for youth.Establish referral support mechanism: Each study site will aim at establishment of referral mechanism for providing adequate care for students at potential high risk. This would be achieved via orienting and engagement with existing district health care service providers and galvanizing capacity building initiatives of health care professionals to respond toward high risk youth.

Following the model optimization, co-development workshops shall be organized with all key stakeholders including, site investigators, officials from state health and education department as well as representatives from the ICMR headquarters. The findings will be discussed for collaborative decision making on implementation strategies and refinement of the most contextually efficient model for scalability (Mref).

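### Effectiveness rests on an uncontrolled 18-month change that ends six months out of calendar phase with baseline, and Phase 1 institutes are not kept out of the cohort

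*Protocol article*

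**What the plan says.** **Outcome.** Primary outcomes defines the reduction in risk factors as a fall over time: "This is measured by a decrease in perceived stress levels and depressive symptoms among students in educational institutions using validated scales". It names no comparator and no time point.

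**Contrast.** The time point comes from Sample size for individual level effectiveness. The difference to be detected is "in mean on the PHQ-9 score in a group (90% power, 2-sided 5% significance level", with "Baseline mean = 8.5; Endline mean = 7.5, SD = 5.0", "assuming a correlation of 0.5 between T1 (Baseline) and T4 scores (3 measurements, 6, 12 and 18 months from baseline". Table 3 (Assessment time-points) confirms "T4 (18 months after T1" and also schedules T3 at 12 months.

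**Risk factors.** Among the socio-environmental drivers of youth suicide, the Introduction lists "exam related factors (e.g., pressure to perform, failure, anxiety".

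**Phases.** Each site runs at least 3–4 optimisation cycles in Phase 1, and in each one "data will be collected on a subsample of 4–6 clusters of educational institutes in the district". For Phase 2: "This phase aims to implement the model (Mref) across all educational institutions over a period of 12–18 months". Table 2 gives Phase 2 its own baseline. No section excludes or flags institutes used earlier.

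**Use of the change.** The cost section (Data analysis) divides incremental cost by the reduction in PHQ-9 and PSS-10. The limitations in the Discussion name Hawthorne effect, recall bias and social desirability. They disclaim attribution only to single components of the model, not to the model as a whole.

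**The concern.** In a before-after comparison without a control, everything else that changes between the two dates is counted with the programme. Two features of this plan make that worse than it need be.

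First, an 18-month interval is one and a half years, so baseline and endline fall at different points of the calendar year whatever the start date. The protocol itself names examination pressure as a driver of risk, so a seasonal component in PHQ-9 and PSS-10 is plausible. The target is only 1 PHQ-9 point (0.2 SD), so a modest seasonal shift could imitate or hide it.

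Second, institutes that took part in Phase 1 would enter Phase 2 with a baseline measured after exposure. That is a different bias: it pulls the measured change towards zero.

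At stake are the effectiveness conclusion and the cost per point of PHQ-9 or PSS-10 reduction, which is built on the same change.

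**Working it through.** **1. The plan's own sample size.** Inputs from the sample-size section: difference 1.0, SD 5.0, correlation 0.5, 90% power, two-sided 5%, 10% non-response.

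- SD of the paired change = 5 × √(2 × (1 − 0.5)) = 5.0.
- n = ((1.960 + 1.282) × 5.0 / 1.0)² = 262.7, so 263; 263 / 0.9 = 293.

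The stated 400 is not reproduced by this one-group formula. It is approached by a two-group comparison of change to the mean of three follow-ups (351, or 390 after non-response), by a two-group ANCOVA at T4 before non-response (395), or by the one-group formula with an unstated design effect of 400 × 0.9 / 263 = 1.37. The point below does not depend on how 400 was reached. For a one-group test, 400 is not too small before clustering.

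**2. Calendar phase.** 18 months − 12 months = 6 months. T3, at 12 months, returns to the same calendar point as T1.

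**3. What a background shift would do.** Completers per stratum: 400 × 0.9 = 360. SE of mean change = 5.0 / √360 = 0.264; with a design effect of 1.37 it is 0.308. The table gives the chance of a two-sided p<0.05 when the programme has no effect. The shifts are assumptions, because the protocol gives no seasonal figure.

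| Assumed shift (PHQ-9 points) | No design effect | Design effect 1.37 |
|---|---|---|
| 0.25 | 16% | 13% |
| 0.5 | 48% | 37% |
| 0.75 | 81% | 68% |
| 1.0 | 97% | 90% |

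A shift in the other direction would mask a real effect by the same amount. Pooling strata or sites would shrink the SE but leave the bias unchanged.

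**4. Prior exposure.** Institutes per site: 64 (Sample size for clusters). Measured change = true change × (1 − exposed share), if exposed institutes have already made their full gain at T1.

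- Same clusters reused in every cycle: 4/64 to 6/64 = 6–9%; a true 1.0 point reads as 0.94–0.91.
- New clusters in each of 3–4 cycles: 3 × 4 = 12 to 4 × 6 = 24, so 12/64 to 24/64 = 19–38%; a true 1.0 point reads as 0.81–0.63.

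The Preparatory phase section speaks of consent from 4–5 clusters for the later phases, which favours reuse and the lower range.

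**5. Timeline.** The study starts on 01.03.2024. Table 2 gives 6 months of preparation and 12 months of Phase 1, so Phase 2 begins about September 2025. T3 then falls about September 2026 and T4 about March 2027. Status and timeline of the study expects data collection to end in December 2026. The cost section (Data collection) already calls 12 months endline, and the projections in Quantitative analysis use 0, 6 and 12 months.

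**The case against.** The strongest reply is that this is implementation research built on RE-AIM and CFIR with a district-led roll-out, so the lack of a control is a legitimate choice. It can be added that the primary time point is less fixed than it looks. Primary outcomes names none, Quantitative analysis describes mixed logistic models on median-split outcomes rather than a T1–T4 mean change, other sections use 12 months, and an analysis plan may settle the matter. Part of this stands: a randomised comparison need not be demanded. But T1 to T4 is the only contrast for which the article sizes the effectiveness sample, and conflicting endlines are a reason to reconcile the sections.

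A reader might go further and infer that endline always sits opposite to baseline in the examination cycle, so that exam season is wholly confounded with the model. The documents do not support that. They give no academic calendar and no T1 dates, the institutes range from grade 9 to postgraduate and professional courses, and baselines may be staggered over eight sites. If examinations were held every semester (an assumption), a six-month offset could return to the same examination phase. Only the calendar offset is certain.

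A reader might also infer that Phase 1 exposure could produce a false benefit, or that the overlap is stated. Neither holds. Overlap is inferred from the coverage of all institutions and the absence of an exclusion. Table 2's wording about a subsample of the selected clusters belongs to the preparatory phase. The effect is dilution, and at the lower range the loss of 0.06–0.09 point is well below the SE of 0.264.

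**Conclusion.** The point holds as two separate weaknesses in an uncontrolled design.

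- **Season and other background change.** The six-month calendar offset is certain; the size and sign of any seasonal shift are unknown. Under the protocol's SD and correlation with 360 completers, an assumed 0.5-point shift alone would be declared significant in about 48% of studies (37% with a design effect of 1.37). A 1-point shift equals the entire planned effect.
- **Prior exposure.** If Phase 1 institutes enter the cohort, the change is probably diluted to 0.91–0.94 of its true size. The figure of 0.63–0.81 needs new clusters in every cycle and full carry-over from 2–3 month cycles of an unfinished model.

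Neither source of bias is acknowledged in the limitations, and nor is the missing comparator. As planned, the study can report how scores changed, but it cannot attribute the change to the refined model.

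**What to change.** (a) Make T1 to T3 the primary effectiveness contrast and keep T4 as secondary. Reconcile the sample-size section and Table 3 with the 12-month endline in the cost section and the December 2026 end of data collection. The visit is already scheduled, and no students are added if the 0.5 correlation also holds at 12 months. The cost is a shorter primary follow-up.

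(b) Draw the effectiveness cohort from institutes not used in the preparatory workshops or Phase 1. Alternatively, flag those institutes and report a sensitivity analysis without them. This is a small change to the sampling rule; because recruitment is under way, flagging may be the easier route.

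(c) State in Primary outcomes, in the cost-effectiveness analysis and in the limitations that the result is change over time without a comparator and is not attributable to the model. This is needed even after (a), which removes the calendar offset but not secular trend or regression to the mean. It costs only wording.

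A randomised two-wave start within sites is optional only. Splitting 360 completers into 180 and 180 gives about 48% power (simple change) to 59% (ANCOVA) before clustering. Depending on the analysis, 90% power would need 390–585 students per group per stratum, again before clustering. A second wave starting about four months later would reach its T3 around January 2027, after data collection is due to end.
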